## Quantitative stage of study

In this stage, the eligible subjects who are interested to participate in the clinical trial will be randomized into intervention or control groups. The target group includes infertile couples undergoing ARTs. The age range of the participants is from 18 to 40 years. They must be able to read and write. It must be their first or second IVF or ICSI session.

## Sample size and sampling method

The sample size is estimate based on similar studies on the lifestyle of infertile couples [24]. The comparison formula between two ratios will be used at the 95% confidence level The Cronbach’s α of 0.05 and power of 80% will be considered. Finally, 600 couples will be included in the study, of which 150 female and 150 males will be placed in the lifestyle program group and the rest in the control group.

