### Sampling, randomization, and blinding methods

After selecting the initial samples, the permuted block randomization will be done using a randomized block design with four blocks by a statistics consultant from a valid website (Sealed Envelope.Com or Randomization.Com). Then, the participants will be divided into two groups per the 1:1 allocation ratio. In this way, after listing all possible situations, 75 blocks of 4 will be created based on the sample size of 300 people. Then, by assigning a number to each of them, using a computerized random number table, with a ratio of 1:1, people will be divided into two intervention and control groups. Then, the subjects will be divided into two intervention and control groups. The numbers are placed in sealed envelopes in the order of each block generated. Each eligible patient who enters the room is then given an envelope. After that, they are assigned to one of these groups. Patient information will be recorded by the research team and confidentiality will be respected.

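### Couples and individuals are mixed up in the sample size: 600 couples, 150 women and 150 men in the programme arm, 1:1 allocation and a 300-person block list cannot all be true

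*Protocol article*

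**What the plan says.** Two sections of the protocol article fix the size of the trial.

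- *Sample size and sampling method*: "Finally, 600 couples will be included in the study, of which 150 female and 150 males will be placed in the lifestyle program group". Everyone else goes to control. On the basis of the calculation, the section says: "The comparison formula between two ratios will be used at the 95% confidence level". It then sets the error level and the power: "The Cronbach’s α of 0.05 and power of 80% will be considered". The section refers to similar studies, but it names no endpoint, proportions or effect size.
- *Sampling, randomization, and blinding methods*: "Then, the participants will be divided into two groups per the 1:1 allocation ratio". On the length of the list, it says: "75 blocks of 4 will be created based on the sample size of 300 people". Envelopes are handed out per eligible patient, not per couple.

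Elsewhere the couple is clearly the intended unit. *Quantitative stage of study* names infertile couples as the target group, and the *Discussion* counts the inclusion of couples rather than individuals as a strength. The main outcomes in the abstract are chemical and clinical pregnancy.

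**The concern.** The two sections give different totals, in different units, and imply different allocation ratios. Pregnancy is observed once per couple, so the number of couples sets the power for that outcome; the number of people does not. Someone who follows the randomisation section word for word could stop at 300 people, which is 150 couples. Someone who follows the sample size section would aim for 600 couples with a list that has 300 places. The envelope instruction adds to the doubt: if each partner counts as a patient, the two members of one couple could draw different arms.

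This is not an effect of condensing a longer document. The article does give the sample size, and the two places where it does so disagree.

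**Working it through.** **Step 1. Counts, using the article's figures only.**

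- 600 couples × 2 = 1,200 individuals.
- Programme arm: 150 women + 150 men = 150 couples = 300 individuals.
- Remainder: 600 − 150 = 450 control couples, so 150:450 = 1:3, against the stated 1:1.
- 600 couples at 1:1 would put 600 / 2 = 300 couples in each arm, not 150.
- Block list: 75 × 4 = 300 allocations, half of the 600 needed at one per couple.
- If 300 means people, the total is 150 couples, or 75 per arm. The 300 members of the programme arm would use up the whole total and leave no control arm.

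**Step 2. Which statements each reading satisfies.**

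| Reading (couples per arm) | 600 couples in total | 150 women + 150 men in programme | 1:1 | 300 allocations, one per couple |
|---|---|---|---|---|
| 150 v 450 | yes | yes | no | no (600) |
| 300 v 300 | yes | no (300 + 300) | yes | no (600) |
| 75 v 75 | no (150) | no (75 + 75) | yes | no (150) |
| 150 v 150 | no (300) | yes | yes | yes |

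No row is free of conflict. The last row fails only on the word couples after 600: 300 couples × 2 = 600 individuals. It also needs the 300 people of the randomisation section to be 300 couples, or one index patient per couple.

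**Step 3. The article's own power figure.** The inputs given are power ("power of 80% will be considered") and 0.05. I read the latter as the significance level, although it is labelled Cronbach's α, and I take it as two-sided from the 95% confidence level. The method is a comparison of two proportions. The proportions are not given, so no sample size can be computed from these inputs and the 80% cannot be reproduced.

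**Step 4. Illustration of what the ambiguity covers.** Every rate here is my assumption. For arms n₁ and n₂ with true rates p₁ and p₂, and p̄ the weighted mean rate:

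Power = Φ{ [|p₁ − p₂| − 1.96 √(p̄(1 − p̄)(1/n₁ + 1/n₂))] / √(p₁(1 − p₁)/n₁ + p₂(1 − p₂)/n₂) }

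Example, 45% v 30% with 150 v 150 couples: p̄ = 0.375. The first root is √(0.375 × 0.625 × 2/150) = 0.0559. The second is √((0.2475 + 0.21)/150) = 0.0552. Power = Φ[(0.15 − 1.96 × 0.0559)/0.0552] = Φ(0.73) ≈ 77%.

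Solving the same formula for the difference that gives 80% power:

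| Couples | Control 20% | Control 30% | Control 40% | Power, 30% v 45% |
|---|---|---|---|---|
| 75 v 75 | 20.9 points | 22.3 | 22.7 | 47% |
| 150 v 150 | 14.3 | 15.6 | 16.1 | 77% |
| 150 v 450 | 11.3 | 12.6 | 13.1 | 91% |
| 300 v 300 | 9.9 | 10.9 | 11.4 | 97% |

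At each assumed control rate, the detectable difference at 75 v 75 is about twice that at 300 v 300.

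**The case against.** The strongest reply is that this is a slip of units with one evident repair. If the patient who receives the envelope is the woman having IVF or ICSI, then 300 people are 300 index patients, one per couple. A 1:1 split then gives 150 women and their 150 partners per arm, exactly as the sample size section says. Only the unit after 600 is wrong. On this view the other rows of the table are misreadings, each ruled out by some other sentence, and the spread in power measures the cost of misreading rather than four live designs.

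Most of this stands. A reader might infer that the counts are irreconcilable, or that the trial could equally be any of four sizes. The documents do not support that, because 150 v 150 fits the arm size, the ratio and the block count together. A reader might also infer that a finished list will run out early, but the article only says that the blocks will be created.

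What does not stand is the idea that the text can be left alone. The repair means changing or reinterpreting the unit in both sections, the article never states it, and the envelope wording does not say that the patient stands for the couple.

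**Conclusion.** The sample size is wrong as written. The contradiction rests on the article's own counts and needs no assumption: 600 couples with 150 in the programme arm is 1:3, against a stated 1:1 and a list of 300 allocations. The likely intention is 300 couples, 150 per arm. That is an inference, and only the sponsor can confirm it.

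A reader might go further and conclude that the 80% power is false or the trial underpowered. The article does not support this. With no proportions or endpoint stated for the calculation, the 80% can be neither confirmed nor refuted, and settling the unit will not by itself make it checkable. The detectable differences (about 14 to 16 points at 150 v 150, 21 to 23 at 75 v 75, 10 to 11 at 300 v 300) depend on assumed control rates of 20% to 40%, a two-sided 5% test and one outcome per couple. They show only that the choice of reading matters.

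**What to change.** The sponsor should confirm the intended number of couples and make the two sections agree.

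- If the reconciling reading is right, *Sample size and sampling method* should give 300 couples (600 individuals), 150 couples per arm. *Sampling, randomization, and blinding methods* should then base the 75 blocks of 4 on 300 couples.
- If 600 couples is intended, the arm sizes and the block list must be corrected instead.
- In either case, name the couple as the unit randomised, with one envelope per couple in place of one per eligible patient.
- Restate the 80% power for the confirmed number of couples, using the endpoint and the two proportions that the sponsor actually assumed. The differences shown above should not be adopted as design assumptions, because they were worked back from the sample size.

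Under the reconciling reading the cost is wording changes in two sections and a stated size of 300 rather than 600 couples. If 600 couples is intended, the list must also be extended to 600 allocations (150 blocks of 4).

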### Registering participants

Clients of the fertility clinics of Akbar Abadi Hospital in Iran University of Medical Sciences will be referred to the research unit after receiving an initial examination by the infertility clinic’s doctors and admitted by infertility midwives or nurses. The study will be described to the consenting participants. The demographic questionnaire and consent form will be completed by the participants and they will ensure of the confidentiality of their information.

### Inclusion criteria

Interest to participate in the research, age range between 18 and 40 years, ability to read and write, Receiving IVF/ICSI for the first or second times.

### Exclusion criteria

Volunteers referred for receiving donor eggs, under treatment for other chronic diseases, sudden surgery or emergency statues, stress and incidents that disrupt the individual’s psychological and nervous status.

## Data collection instruments

The participant’s information will be collected using approved standard questionnaires. The Health Promoting Lifestyle Profile-II (HPLP-II) is the questionnaire that employed to determine the life status before and after the intervention. It was developed by Walker [32] and its validity and reliability are validated by Mohammadi et al., in Iran [33]. Stress and anxiety will be measured using Beck’s standard inventory [34], and it is validated by Mohammadkhani in Iran [35]. The IPAQ will be employed to measure the physical activity status [36, 37]. The frequencies with which food items are consumed will be assessed using the Food Frequency Questionnaire (FFQ) [37, 38]. Finally, the demographic information will be obtained by a researcher-made demographic questionnaire containing items related to age, weight, height, BMI, occupation, miscarriage, stillbirth, etc. The questionnaire will be completed at the beginning of the first visit. The subsequent assessment will be carried out within the specified time that will choose in expert panel after the intervention.

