**Methodology/Design:**

This study entails three steps. The first step includes the systematic review of literature on a health-promoting lifestyle in infertile couples undergoing ARTs, a systematic review of observational studies and interventions in couple’s lifestyle, then, a systematic review of qualitative studies on infertility in couples and their lifestyle, and in the final step couple’s life style literature systematically will evaluate in Iran. In case of failure to obtain the required results from systematic reviews, cross-sectional studies will be carried out to determine the lifestyle of infertile couples receiving ARTs. In the second stage, by holding a panel of experts, an intervention is planned based on the results of the previous stages in order to improve the lifestyle of couples. In the final step, the designed intervention will be administered as a random clinical trial—on ART candidates, in intervention or control groups in one of Iran University of Medical Sciences hospitals. Afterward, the data’s will be evaluated by using standard questionnaires, that include health-promoting lifestyle questionnaire (HPLII), Beck’s depression inventory (BDI), international physical activity questionnaire—short form (IPAQ-SF), and food frequency questionnaire (FFQ). The statistical analysis will be carried out in SPSS software. During the study, subjects meeting the inclusion criteria were randomly selected and randomized into the intervention and control groups. The health-promoting lifestyle training program will be executed for the intervention group while the standard care program is administered to the control group. The content of this program will be obtained from the consensus opinions of the expert panel. The program includes diet recommendations, physical activity, and stress management. Appropriate time, frequency, duration and number of activities will be considered. Communication with subjects will be possible through private meeting special comfort room. Support to the participants will also be through clinical visits social media, SMS and phone calls. Nutritional changes, physical activity amount, anxiety and stress level, abdominal circumference (AC), and body mass index (BMI) will be measured after the completion of the specified time interval. The initial outcome includes examining chemical pregnancy (2 weeks after the transmission) and clinical pregnancy by ultrasound (6 weeks after). The secondary outcome will be live birth rate. Retrieved oocyte and embryo numbers will also be reported.

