## Background

Amongst all steps in the lifecycle of a living creature, the highest evolutionary pressure is exerted on the process of fertility [1]. The most recent reports indicate a decrease in the live birth rate [2]. Considering the rising rate of infertility [3] and the need to use ART, lifestyle factors are more emphasized. The WHO defined infertility as a disease in the male or female reproductive system, which failed to achieve pregnancy after 12 months of unprotected sexual intercourse. In total, 186 million people and 48 million couples are infertile worldwide [4]. Infertility has destructive social and health consequences including social stigma, economic problems, and poor physical and mental well-being [5]. Following a meta-analysis report, the lifetime prevalence of infertility amounted to (3.3–21.3%) in the Eastern Mediterranean Region, 7% in England, and 30% in African countries [4, 6]. The population problem is a fundamental issue concerning policy-making and future planning. Based on the 2019–2020 censuses, the total fertility rate in Iran decreased to 1.2 children per woman. Taking into account the current fertility process, the population growth will approach zero between 2036 and 2041 [7]. ART comprises all methods in which oocytes, sperms, and embryos are directly manipulated outside the body in in-vitro. The first and most common form of ART is in vitro fertilization (IVF) [8]. The effects of lifestyle on infertility shown in the accumulated data from various studies suggest that such factors as smoking, depression, and anxiety can contribute to infertility [4]. Furthermore, mounting evidence indicated that obesity, an imbalanced diet, and a lack of physical activities play a crucial role in infertility causes [9]. Recent studies pointed out that inflammation in the body can cause damage to Germ cells. Following a diet rich in antioxidants, flavonoid resources, and unsaturated fatty acids, and decreasing the consumption of red meat, particularly processed meats, are effective in reducing inflammation. Sticking to a proper diet before pregnancy is an effective key solution [10]. Food-based dietary guidelines (FBDG) recommend reducing the sugar and saturated fat intake and increasing the use of unsaturated fat, seeds, whole grains, fruits, and fish [11]. The Mediterranean diet (MD) is one of the healthiest and most beneficial diets in the world. Food intake pattern in this diet includes large amounts of pulses, seeds, whole grains, fruits and vegetables, median intake of fish and wine, and low intake of dairy products and red meat. Fat intake resources are olive and olive oil. This diet is a rich source of unsaturated fats, fibers, antioxidants, and the minimum amount of saturated fats [12]. Vojokovic conducted a study in the Netherlands on the relationship between dietary styles and infertility and identified two dietary patterns. The first pattern (health conscious–low processed) emphasizes the high intake of fruits, vegetables, whole grains, and seeds and the low intake of processed foods, such as Mayonnaise, snacks, and meat products [13]. Noori’s study suggested that dairy consumption affects sperm parameters, whereas the consumption of saturated fats and calcium resulted in poor-quality sperm. On the other hand, the consumption of high amounts of folate and selenium, plus low consumption of cholesterol has a positive impact on the improvement of sperm parameters [14]. In their study, Xiao Cheng indicated that healthy diet adjuvant therapy, Mediterranean diet (MD), Ketogenic diet (KD), and dietary approaches to stop hypertension (DASH) were effective on fertility results [15]. Results of some studies demonstrated the impact of a sedentary lifestyle, and as a result, low health-related quality of life (HRQoL) on infertile people. Furthermore, high BMI and the increase in anxiety and stress affect HRQoL [16]. Even though exercise is regarded as a general improving factor, excessive exercise has an unpleasant and inhibitor impact on the hypothalamic–pituitary–adrenal axis (HTP axis). In the study by Minas, exercise reduced oxidative stress and improved chronic inflammation by increasing antioxidant defense in the testes. In addition, it decreased obesity, diabetes, and infertility rate [17]. The effective factors on the well-being and health of women with primary infertility were investigated in India and factors, such as psychological problems, duration of infertility, insufficient physical activity, education level, sleeping pattern, and family structure were shown to be crucially important in infertility [18]. The study by Palomba on 216 women under the treatment by IVF/ICSI revealed that regular physical activity before fertilization procedure improves fertility outcomes in infertile obese women [19]. Gaskin in the study of environment and fertility health (EARTH) examined the physical activity in 427 women under IVF treatment. The results showed that 2.8 h of average or severe physical activity per week has no significant impact on embryo implantation, clinical pregnancy, and live birth. However, women performing activities, such as aerobics, skiing, and boating had a higher rate of live birth [20]. In addition to the impact of exercise and physical activity on general health and fertility, it is quite clear that the type of food and diet styles is amongst the crucially important pillars of a healthy life, mental and psychological health, and psychological issues. Diagnosis of infertility is followed by comprehensive anxiety and stress and causes consequences, such as depression, unhappiness, guilty feeling, low self-esteem, destroyed self-confidence and inability to overcome obstacles and problems [21]. Research reported the anxiety rate caused by infertility amounts to approximately 75.9% in women and 60.6% in men. This high anxiety level and stress pressure affects couples’ fertility health [22]. Regardless of the impact of infertility on the stress and anxiety rate, IVF/ICSI procedures can cause stress and anxiety. Supporting couples in this step and providing them with the required stress and anxiety management training helps improve the quality of their life and increase the possibility of achieving their valuable wish’s goal [23]. Numerous factors affect lifestyle. Health-promoting lifestyle includes the following six dimensions: diet, exercise, stress management, health responsibility, interpersonal relationships, and spiritual growth leading to self-actualization. Lifestyle refers to all behaviors controlled by the individual, or behaviors that affect personal health risk factors [24]. A comprehensive approach suggests that health-protective behaviors (HPB) (risk reduction and prevention) and health-promoting behaviors can be regarded as two supplementary components of a healthy lifestyle. These behaviors, improve the health, self-actualization, and psychological maturity ‏of individuals. The European Society of Human Reproduction and Embryology (ESHRE) guideline argues that multipurpose programs in various fields are crucial to meet cognitive, communicative, and mental-psychological needs, as well as consultation concerning lifestyle [25]. Doomar conducted a study on 12,800 infertile women and found that IVF candidates have habits, such as smoking, drinking coffee and alcohol, having a sedentary lifestyle, and the use of recreational or unauthorized drugs [26]. Studies in Iran showed the prevalence of psychological disorders including depression, hypochondriasis, and paranoia among infertile couples [27], and these groups exhibited a high tendency toward unhealthy and Western nutrition [28]. Furthermore, the increase in exercise in women with IVF pregnancy was associated with a significant decrease in gestational diabetes and pre-eclampsia [29]. In the study by Baheiraei on the lifestyle of infertile couples, negligence towards a healthy lifestyle, particularly among men, indicates that this group needs appropriate health protection training programs before carrying out infertility treatments, as well as during and after IVF interventions [30]. A tailored literature-based program includes nutrition, physical activity, and exercise, together with stress reduction in the course of IVF/ICSI interventions. Similar integrated studies that include a combination of various health dimensions have rarely been conducted in Iran. The necessity of these programs in fertility clinics before beginning any medical treatment or procedure concerning the fertilization procedures is sensed and their absence can affect fertilization outcomes. It is hoped that this study can improve fertilization outcomes by promoting couples’ lifestyles.

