
## Aims of study

The main aim of the study in the first stage is to design a lifestyle intervention program in infertile couples receiving assisted reproductive technologies (ART). Then studies on the lifestyle of couples undergoing IVF/ICSI treatment will be identified and investigated. Choosing a suitable and beneficial program to promote health in men and women will be examined. After that, lifestyle risk factors (e.g., the lack of physical activity, unhealthy diet, consumption of fast foods and processed foods, weight gain and obesity, consumption of alcohol and coffee, smoking, use of other stimulants and narcotic drugs), psychological pressure complications (e.g., depression, stress, and anxiety), the lack of adequate alleviating training to manage stress and anxiety, sleep disorders, insomnia and sleep hygiene in couples will be investigated and studied. In the next step, an intervention will be executed and its effectiveness will be determined (Fig. 1).

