## Abbreviations

ART: Assisted reproductive technique
IVF: In vitro fertilization
ICSI: Intra cytoplasmic sperm injection
HPLII: Health promoting lifestyle II
BDI: Beck depression inventory
FFQ: Food frequency questionnaire
IPAQ: International physical activity questionnaire
NCD_S_: Non communicable diseases
FBDG: Food based dietary guideline
SPSS: Statistical Package for the Social Sciences
DASH: Dietary approach to stop hypertension
ESHRE: European Society of Human Reproduction and Embryology
SPIRIT: Standard Protocol Items: Recommendations for Interventional Trials

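### The only Beck instrument the protocol identifies is the depression inventory, yet it is assigned to stress and anxiety, and no scale for either is named

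*Protocol article*

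**What the plan says.** The Abstract (Methodology/Design) lists four questionnaires: a health-promoting lifestyle questionnaire, then "Beck’s depression inventory (BDI), international physical activity questionnaire—short form (IPAQ-SF", and a food frequency questionnaire. It also says that, once the set interval has passed, "anxiety and stress level, abdominal circumference (AC), and body mass index (BMI) will be measured", along with nutrition and physical activity. Stress management is one of the three programme components it names.

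The Data collection instruments section goes through four questionnaires in the same order and gives the second one its purpose: "Stress and anxiety will be measured using Beck’s standard inventory [34". The lifestyle profile (HPLP-II) has a different purpose there; it "is the questionnaire that employed to determine the life status before and after the intervention".

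The Abbreviations contain one Beck entry, "BDI: Beck depression inventory". The Aims of study list "psychological pressure complications (e.g., depression, stress, and anxiety" among the matters to be investigated.

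**The concern.** An outcome can only be reported as what its instrument measures. The Abstract promises a result on anxiety and stress, while the only Beck questionnaire identified by name measures depression. The Aims of study treat depression as a different condition from the other two.

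Two misreadings could follow. A fall in anxiety or stress without a change in depressive symptoms could go undetected. A change in depressive symptoms would be labelled as a change in anxiety and stress. In either case the trial would lack evidence on whether the programme altered the states that its stress-management component is aimed at.

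**Working it through.** No arithmetic applies. The point depends on no sample size, error rate or event count, and the plan gives no figure to reproduce. The check is to set every statement about the Beck instrument, and about anxiety, stress and depression, side by side.

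| Place in the protocol article | What it fixes |
|---|---|
| Abstract, list of questionnaires | Beck instrument is the depression inventory: "Beck’s depression inventory (BDI" |
| Abstract, measurements after the intervention | Anxiety and stress level is measured; depression is not in this list |
| Aims of study | Depression, stress and anxiety are three separate items |
| Data collection instruments | A Beck inventory, type not stated, measures stress and anxiety |
| Data collection instruments | HPLP-II measures life status |
| Abbreviations | BDI is the only Beck entry; no anxiety or stress scale is listed |

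**Step 1: which Beck inventory?** The sentence in Data collection instruments does not say. The Abstract and the Abbreviations each name the depression inventory. The two lists of four questionnaires run in the same order (lifestyle profile, Beck, physical activity, food frequency), so the second item is most naturally the same instrument in both. This is an inference. The cited source is not available to confirm it.

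**Step 2: if it is the depression inventory.** The assigned constructs are stress and anxiety; the measured construct is depression. Neither assigned construct has an instrument, and the construct that is measured is missing from the Abstract's list of post-intervention measurements.

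**Step 3: if it is a Beck anxiety inventory.** Anxiety is then covered, but the Abstract and the Abbreviations name the wrong questionnaire. Stress still has no scale of its own.

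**Step 4: does another questionnaire fill the gap?** The physical activity and food frequency questionnaires do not bear on it. HPLP-II comes closest, since the Background says "Health-promoting lifestyle includes the following six dimensions: diet, exercise, stress management" and three further dimensions. Stress management in that list is a health behaviour, not a level of stress, and anxiety is not among the six dimensions.

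On both readings at least one of the two named states has no instrument, and at least one section has to be corrected.

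**The case against.** **The inventory is not shown to be the depression inventory.** A reader might infer that the protocol plainly states it will measure anxiety with a depression scale. It does not: the key sentence leaves the inventory unspecified, and a different Beck instrument may have been intended. This stands as a limit on certainty. It does not remove the point, because the other reading makes two sections wrong and leaves stress without a scale.

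**HPLP-II touches stress management before and after the intervention.** That is true as a measure of lifestyle. The protocol does not assign it to the level of stress or anxiety, so it does not supply the missing instrument.

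**An article condenses a fuller protocol.** Missing detail would be no finding. Here, however, the article states which instrument measures which construct, and that statement conflicts with its own Abstract and Abbreviations.

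**The outcome ranks low.** This stands. The Abstract makes chemical and clinical pregnancy the initial outcome and live birth the secondary outcome. The Third stage objective names oocytes, sperm parameters, pregnancy and live birth, but not anxiety or stress. A reader might infer that a programme which lowers anxiety would be reported as having no effect. The documents do not support that, because the programme is judged on pregnancy and live birth.

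**A late correction would not lose everything.** This also stands. A reader might infer that the fault could never be repaired once baseline has passed. Yet the Data analysis section plans an independent-groups t-test, and with randomised arms a post-intervention comparison is valid without a baseline score. What would be lost is change from baseline, and some precision, for participants already assessed. The sentence on completing the questionnaire at the first visit also follows directly on the demographic form, so it is unclear which questionnaire it covers.

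**Conclusion.** The point holds as a mismatch between the stated outcome and the only Beck instrument identified. As written, anxiety and stress level would be reported from a depression score, and the trial could not show whether the programme changed either state. If a Beck anxiety inventory was meant, the fault becomes a wrong name in the Abstract and Abbreviations plus an unmeasured stress outcome.

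The whole anxiety and stress measure is affected, in both arms. It is an intermediate outcome; the pregnancy and live birth comparisons are unaffected. The conclusion rests on the article's own wording and on the assumption that no further questionnaire is used beyond the four it lists. That the Beck inventory is the depression inventory is likely but not proven; that the sections need reconciling does not depend on it.

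**What to change.** Before the first baseline assessment:

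1. Name the exact Beck inventory and version, and make the Abstract, Data collection instruments and Abbreviations agree. This is a change of wording only.
2. Then choose one of two courses.
   - Use a validated anxiety scale and a validated perceived-stress scale, each named as its own outcome. If a Beck anxiety inventory was intended, it can fill the first role and only a stress scale has to be added. The cost is one or two short questionnaires, a few minutes per participant per assessment. This keeps the trial's own question.
   - Keep only the depression inventory, rename the outcome as depressive symptoms in the Abstract and in Data collection instruments, and drop the claim about anxiety and stress. The cost is a narrower claim. This course is right only if step 1 confirms that the depression inventory was meant.

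The expert panel has still to set the programme and the time of the later assessment, so the choice of instrument can be settled alongside them.
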